## 1 Introduction

Type 1 diabetes (T1D) affects around 400,000 people in the UK and is caused by nearly complete loss of insulin-producing cells in the pancreas. It is often challenging to achieve good control of blood glucose throughout the day in T1D, in part because of fluctuations associated with giving insulin. Severe episodes of low blood sugar levels, commonly called “hypos”, are one of the most feared complications of managing diabetes with insulin.

The impaired release of other hormones, such as plasma glucagon which raises blood sugar, during hypo episodes is also part of type 1 diabetes. A better understanding of this mechanism could lead to treatments aimed at reducing the risk of hypoglycaemia.

Glibenclamide is an oral anti-diabetic medication (sulfonylurea) which is commonly used to increase the amount of insulin released by the pancreatic beta-cells. Recent pre-clinical studies have shown that sulfonylureas can also improve plasma glucagon levels when used in very small doses by working on pancreatic alpha-cells, which release plasma glucagon. We have previously conducted a pilot study (LEGEND-A), which suggested that low doses of glibenclamide (0.3mg/day) could alter plasma glucagon release in some people with type 2 diabetes without increasing the risk of hypoglycaemia. In addition, another type of oral anti-diabetic medication, called dapagliflozin, has also been shown to work on pancreatic alpha-cells.

Therefore, the aim of this follow-up study (LEGEND-D) is to find out whether similar doses of glibenclamide or a single dose of dapagliflozin could increase plasma glucagon release in people with T1D. We hope that add-on therapies such as these may become a new way of helping people with T1D to prevent hypoglycaemia.

The trial will involve 2 groups of participants:

- a) 20 people with T1D, who will be given a liquid form of glibenclamide orally for a maximum of 54 days (at 3 different doses, in 3 blocks of 14-18 days), followed by a single oral dose of dapagliflozin, and undergo 5 controlled hypoglycaemia challenges.
- b) A control group of 10 people without diabetes, who will undergo one hypoglycaemia challenge without receiving any medication.

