**Table 1 : Definition of hypoglycaemia**

|                |                                                                                                                       |
|----------------|-----------------------------------------------------------------------------------------------------------------------|
| Level 1 | < 4.0 mmol/L (70mg/dL) = glucose alert                                                                         |
| Level 2 | < 3.0 mmol/L (54mg/dL) = clinically important hypoglycaemia                                                    |
| Level 3 | <4.0 mmol/L with severe cognitive impairment requiring external assistance for recovery = severe hypoglycaemia |

4.To compare the change in plasma glucagon from euglycaemia to hypoglycaemia in T1D participants prior to and following administration of a single 10 mg dose of oral dapagliflozin, to that of participants without diabetes (non-DM group).

5.To compare the change in plasma somatostatin from euglycaemia to hypoglycaemia in T1D participants prior to and following administration of a single dose of dapagliflozin 10mg, to that of participants without diabetes (non-DM group).

6.To characterise the development of hypoglycaemic symptoms during induced hypoglycaemia at baseline, and during each dose of glibenclamide and dapagliflozin.

7.To measure any residual C-peptide participants with T1D only.

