## 1.2 Study Design

The LEGEND-D trial is a pilot, randomised cross-over, single-centre, non-blinded, clinical trial which aims to investigate the effect of 3 low doses of glibenclamide (0.3mg, 0.6mg and 3mg/day) assigned in all possible sequences followed by dapagliflozin (single dose of 10mg) on the plasma glucagon response during induced hypoglycaemia in people with type 1 diabetes, compared to non-diabetic individuals (**Figure 1**). The trial will be conducted by the Oxford Centre for Diabetes, Endocrinology and Metabolism (OCDEM) Clinical Research Unit (CRU) at the Churchill Hospital.

**Figure 1:** Trial flow chart

[figure not shown]

A summary timeline of the trial is shown on figure 1 above. For participants with T1D, the trial is divided into 5 steps, and involves 5 hyperinsulinaemic hypoglycaemic clamps. Once step 1 (no medication) has been completed, the participants with T1D will be randomised to a sequence of glibenclamide doses for the subsequent steps, followed by a single dose of 10mg dapagliflozin. There will be a washout phase of at least 48 hours between each step (the half-life of the glibenclamide suspension is 8 hours) [1]. Participants without diabetes will undergo a single hyperinsulinaemic hypoglycaemic clamp, as they will not receive any study medication.

The total daily dose as defined by the dosing schedule will be split into AM and PM as shown in

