### **1.3 Participants Identification**

#### **1.3.1 Trial Participants**

The anticipated recruitment period is 12 months; the recruitment target is 20 participants with T1D and 10 non-DM controls. The study will aim to include participants of different age groups.

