### **1.3.4 Sample Size Determination**

There are currently no data on plasma glucagon levels from human trials using low-dose sulfonylureas in patients with type 1 diabetes. The sample size calculations are based on the data generated from the LEGEND-A trial [4] (NCT02830048 - completed) and interim analysis from the DEPTH trial (NCT03537131 – suspended due to the COVID-19 pandemic).

The LEGEND-A trial suggested glibenclamide (at a dose of 0.3mg/day) could change plasma glucagon levels in participants with type 2 diabetes by 30% (magnitude of effect), while the DEPTH trial suggested that participants with type 1 diabetes who experienced exercise-induced hypoglycaemia had mean plasma glucagon values of 5.54pmol/L (SD 2.14pmol/L) at the time of hypoglycaemia (defined as <3.3mmol/L).

For the non-diabetic control group, data from a clinical study in healthy volunteers [5], which used similar methodology and a plasma glucagon assay comparable to the one we will use in our trial, demonstrated that the mean plasma glucagon values during the hypoglycaemia plateau of 23.3 pmol/L (SD 5.7pmol/L).

These figures indicate that 20 participants with T1D, and 10 participants without diabetes (including 5% dropout) would give the LEGEND-D trial 80% power to detect a 30% increase in plasma glucagon levels (the primary endpoint) during induced hypoglycaemia (hyperinsulinaemic-hypoglycaemic clamp).

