## 2.2 Exploratory Endpoints

### 2.2.1 Definitions and Derivation of Exploratory Endpoints

Exploratory efficacy endpoints are defined as the difference between measurements (defined below) at baseline and at post treatment period (i.e. 0, 15, 30 and 40min):

- Plasma glucagon level is the concentration of plasma glucagon measured in pmol/L.
- Plasma somatostatin level is the concentration of plasma somatostatin measured in pmol/L.
- Blood glucose value is the concentration of blood glucose measured in mmol/L.
- Plasma C-peptide level is the concentration of plasma C-peptide measured in pmol/L.

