6. To characterise the development of hypoglycaemic symptoms by listing self-reported hypoglycaemia symptoms and recording blood glucose value (mmol/L) at onset of self-reported hypoglycaemia symptoms (see **Table 4**[Error! Reference source not found.](#): Assessment of hypoglycaemia symptoms) during the induced hypoglycaemia at baseline, and during each dose of glibenclamide (at 0.3mg, 0.6mg or 3mg) and dapagliflozin.

A multilevel modelling approach (treatment x group) will be used to compare the onset of self-reported hypoglycaemic symptoms during the hyperinsulinaemic hypoglycaemic clamp between the group with and without diabetes.

7. To measure fasting plasma C-peptide levels (pmol/L) at the start of the hyperinsulinaemic hypoglycaemic clamp (T1D group only).

We will use descriptive statistics to describe fasting plasma C-peptide levels (pmol/L) at the start of the hyperinsulinaemic hypoglycaemic clamp (T1D group only). This will be in the form of mean (standard deviation) if data is normally distributed or median (interquartile range) if not normally distributed.

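### The planned C-peptide summary (SAP 5.4.1 item 7) cannot show how many T1D participants have residual C-peptide, and section 2.2.1 defines the endpoint differently

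*SAP*

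**What the plan says.** Objective 7 in SAP section 1.1.2 (printed below Table 1) reads: "To measure any residual C-peptide participants with T1D only". Its analysis is item 7 of section 5.4.1. The sampling point is given as "To measure fasting plasma C-peptide levels (pmol/L) at the start of the hyperinsulinaemic hypoglycaemic clamp (T1D group only", and the summary rule is: "This will be in the form of mean (standard deviation) if data is normally distributed or median (interquartile range) if not normally distributed". The SAP plans no other analysis for this objective. It gives no count of participants with measurable C-peptide, no cut-off, no assay limit and no rule for values below one.

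Three other places bear on the point:

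- Section 2.2.1 lists plasma C-peptide among endpoints introduced by: "Exploratory efficacy endpoints are defined as the difference between measurements (defined below) at baseline and at post treatment period (i.e. 0, 15, 30 and 40min".
- Section 1.2 states that for T1D participants "the trial is divided into 5 steps, and involves 5 hyperinsulinaemic hypoglycaemic clamps". One clamp is untreated, three are on glibenclamide and one follows dapagliflozin.
- Section 5.2 has outcome variables summarised for each treatment period and names C-peptide as a baseline variable. The Table 5 shell gives C-peptide both a mean (SD) line and a median (Q1-Q3) line, with a T1D column.

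**The concern.** The SAP's Introduction describes type 1 diabetes as an almost total loss of insulin-producing cells. A plausible C-peptide distribution is therefore a cluster of very low values with a few higher ones. That shape is not normal, so item 7 would select the median and IQR, which describe the middle half of the group. Residual secretion, if present, would sit in the upper tail, where neither figure looks. The chosen summary is thus insensitive to the feature the objective names.

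Two wording problems add to this. Item 7 refers to a single clamp when there are five, and the Introduction describes glibenclamide as "commonly used to increase the amount of insulin released by the pancreatic beta-cells", so a value taken on that drug is not the same quantity as an untreated one. And section 2.2.1 and item 7 describe different C-peptide endpoints.

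At stake is how well the trial can describe its own T1D group on this feature. No hypothesis test depends on it.

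**Working it through.** The SAP states no C-peptide figure, so there is nothing to reproduce. The check asks what the planned summary would print.

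**Inputs.** n = 20, from section 1.3.1: "the recruitment target is 20 participants with T1D and 10 non-DM controls". The 5% dropout allowance, from section 1.3.4 ("20 participants with T1D, and 10 participants without diabetes (including 5% dropout"), gives 20 × 0.95 = 19. Assumptions: participants without residual secretion share one floor value (set to 0; any common floor gives the same pattern), and k participants have measurable values (100 pmol/L as a placeholder).

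**Which branch of the rule applies.** With k = 4 and the measurable values drawn between 20 and 200 pmol/L, a Shapiro-Wilk test gives p of about 3 × 10⁻⁷; with k = 1, about 3 × 10⁻⁹. The SAP names no normality test, but any reasonable one would reject, so median (IQR) is used.

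**Where Q3 falls.** By linear interpolation, Q3 sits at position 1 + 0.75 × (20 − 1) = 15.25, between the 15th and 16th ordered values. With k measurable values, the first 20 − k are at the floor, so the 16th leaves the floor only when k is at least 5. Results under nine standard quantile definitions:

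| n | k | Median | Q3 |
|---|---|---|---|
| 20 | 0 to 4 | floor | floor under all nine |
| 20 | 5 | floor | above floor under six of nine |
| 20 | 6 | floor | above floor under all nine |
| 19 | 4 | floor | floor under all nine |
| 18 | 3 | floor | floor under all nine |
| 18 | 4 | floor | floor under six of nine |

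The result for k = 0 to 4 at n = 20 does not depend on the placeholder, because those values never enter Q3.

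**What Table 5 adds.** With four participants at 100 pmol/L, the mean is 4 × 100 / 20 = 20.0 and the SD is √[(4 × 80² + 16 × 20²) / 19] = √(32,000 / 19) = 41.0. That is visibly above the floor. It does not give the number of participants, as two invented sets show:

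- Two participants at 200: mean 400 / 20 = 20.0; SD = √[(80,000 − 20 × 20²) / 19] = √(72,000 / 19) = 61.6.
- Four participants at 273, 50, 40 and 37: mean 400 / 20 = 20.0; sum of squares 74,529 + 2,500 + 1,600 + 1,369 = 79,998; SD = √[(79,998 − 8,000) / 19] = 61.6.

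Both also have median (Q1-Q3) at the floor, so every C-peptide figure in the T1D column of Table 5 is the same for 2 of 20 and for 4 of 20.

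**What a count would show.** Exact (Clopper-Pearson) 95% limits: for 0/20, 0% to 1 − 0.025^(1/20) = 16.8%; for 4/20 = 20%, the 2.5% point of Beta(4, 17) and the 97.5% point of Beta(5, 16), that is 5.7% to 43.7%.

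**The two definitions side by side.** Section 2.2.1: a difference between baseline and post-treatment, at 0, 15, 30 and 40 min. Item 7: a fasting level at the start of a clamp, described and not differenced. No part of section 5.4 analyses the former for C-peptide. This mismatch needs no assumption about the data.

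**The case against.** A reader might infer that the trial would report no residual C-peptide when up to a fifth of the group has it. The SAP as a whole does not support that. A median at the floor is not a statement of absence, and the baseline mean (SD) in Table 5 would sit above the floor. What stands is narrower: the planned output does not say in how many participants C-peptide is present.

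A reader might also infer that values taken on glibenclamide would be pooled with untreated ones. Section 5.2 plans summaries by period and a baseline table, so an untreated summary is foreseen and pooling is not planned. The remaining gap is that item 7 does not name the clamp that answers the objective.

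The common floor is an assumption. Eligibility requires only 12 months since diagnosis, and the SAP gives neither an assay limit nor a distribution. If low values are reported as measured, the quartiles will not collapse to one number. Even then, Q3 depends only on the 15th and 16th values, so the sizes of the top four remain unseen.

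The objective speaks of measuring residual C-peptide, and turning it into a yes-or-no question is an interpretation. It is fair to say that a level summary measures something. But the word any in the objective makes the number of participants the natural companion result.

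Finally, nothing in the SAP supports a claim that C-peptide would explain who responds: the hypothesised mechanism concerns alpha-cells and no subgroup analysis is planned.

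**Conclusion.** The point holds as a minor one. Given a common floor and n = 20, item 7's median (IQR) is identical for 0 and for 1 to 4 participants with measurable C-peptide (0% to 20%) under every standard quartile definition. With 19 participants, 4 are still hidden. Table 5's mean (SD) softens this but does not supply the count. Two defects stand regardless of the floor assumption: item 7 leaves the clamp unnamed, and section 2.2.1 conflicts with item 7 and describes a C-peptide difference that is never analysed. The item is exploratory and descriptive, and the primary glucagon analysis is unaffected.

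**What to change.** - In section 5.4.1 item 7, make the headline result the number (%) of T1D participants, with exact 95% CI, whose fasting C-peptide at the untreated step 1 clamp is at or above the assay's lower limit. State that limit and how values below it are handled.
- Give the maximum and a listing of individual values. The median (IQR) can stay as a secondary summary.
- Add the count row to Table 5.
- Show clamp-start values from later steps separately by step.
- Align section 2.2.1 with item 7: either remove C-peptide from the 0 to 40 min difference, or keep it only as the change in fasting value by step.

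The cost is SAP wording, one table row and one listing. It uses values the SAP already plans to collect and needs no new participants.

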#### 5.4.2 Sensitivity and Exploratory Analyses

Exploratory analyses for efficacy will be carried out. No sensitivity analysis is planned for exploratory endpoints.

#### 5.4.3 Subgroup Analyses

No subgroup analyses are planned.

#### **5.4.4 Safety Analysis**

1. To measure the frequency of adverse events in participants treated with Glibenclamide and Dapagliflozin at each study visit.

Descriptive statistics in form of percentages will be used to determine the proportion of adverse events.

Summary tables for adverse events will include the following:

- Counts (percentage) of subjects with any AEs by treatment and sequence.
- Counts (percentage) with any TEAEs by treatment and sequence.
- Counts (percentage) of subjects with any related TEAEs (AR) by treatment and sequence
- Counts (percentage) of subjects with any serious TEAEs (SAE) by treatment and sequence
- Counts (percentage) of subjects with any related serious TEAEs (SAR) by treatment and sequence

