### 1.1.3 Safety Objectives

1. To measure the frequency of adverse events in participants treated with Glibenclamide and Dapagliflozin.

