### 2.2.2 Definitions and Derivation of Safety Endpoint(s)

Safety endpoint is defined as number of adverse events during treatment period of glibenclamide (at 0.3mg, 0.6mg or 3mg) and dapagliflozin **Table 4**.

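### The safety endpoint counts adverse events, but the listed safety tables count subjects over unequal treatment windows with no time at risk

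*SAP*

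**What the plan says.** Section 2.2.2 sets the endpoint in units of events: "Safety endpoint is defined as number of adverse events during treatment period of glibenclamide (at 0.3mg, 0.6mg or 3mg) and dapagliflozin". Section 1.1.3 words the objective in the same spirit: "To measure the frequency of adverse events in participants treated with Glibenclamide and Dapagliflozin". Section 5.4.4 repeats that objective and adds that it applies at each study visit.

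Section 5.4.4 then gives the method: "Descriptive statistics in form of percentages will be used to determine the proportion of adverse events". It does not say what the denominator of that proportion is. Five summary tables follow, for any AE, any TEAE, related TEAEs, serious TEAEs and related serious TEAEs, all by treatment and sequence. The first reads "Counts (percentage) of subjects with any AEs by treatment and sequence". The second reads "Counts (percentage) with any TEAEs by treatment and sequence"; it drops the reference to subjects, but its wording still points to subjects with at least one event. The other three name subjects expressly.

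On exposure, section 1 says that T1D participants receive glibenclamide "at 3 different doses, in 3 blocks of 14-18 days), followed by a single oral dose of dapagliflozin". Section 1.2 adds that the dapagliflozin dose is taken at the start of the final clamp visit and that steps are separated by a washout of at least 48 hours.

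**The concern.** There are two separate problems.

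The first is a mismatch of unit. A participant with one event on a dose and a participant with ten contribute equally to a count of subjects with any event. If repeat events rose with dose, the listed tables would not show it, although the endpoint as defined would.

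The second is unequal observation time. The chance of at least one event grows with the length of the window. Placing a 14-18 day block beside a single dose, with no time at risk shown, invites a reader to take the lower dapagliflozin percentage as a safety advantage when part or all of it may reflect shorter observation.

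**Working it through.** **Step 1: endpoint against output.**

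| Place in SAP | Unit |
|---|---|
| 1.1.3, objective | frequency of adverse events |
| 2.2.2, endpoint | number of adverse events per treatment period |
| 5.4.4, method | proportion of adverse events, no denominator named |
| 5.4.4, five tables | subjects with any event of the given type |

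No listed table gives a number of events, and none matches the reference to each study visit. Nothing elsewhere fills the gap. Section 2.2.2 points to Table 4, which is a checklist of hypoglycaemia symptoms, and the only results template in the appendix is for baseline characteristics.

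**Step 2: effect of unequal windows.** The SAP gives no adverse event rate and no safety sample size calculation, so there is no figure of its own to reproduce. What follows is an illustration.

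Inputs from the SAP: 14 to 18 days per glibenclamide dose, one dapagliflozin dose, and 20 T1D participants. Assumptions: the same constant daily risk p on both drugs, 1% or 3%, and a dapagliflozin window of 1 or 3 days.

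Formula: P(any AE in d days) = 1 − (1 − p)^d.

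| d (days) | p = 1% | p = 3% |
|---|---|---|
| 1 | 1.0% | 3.0% |
| 3 | 1 − 0.99^3 = 3.0% | 1 − 0.97^3 = 8.7% |
| 14 | 1 − 0.99^14 = 13.1% | 1 − 0.97^14 = 34.7% |
| 18 | 1 − 0.99^18 = 16.5% | 1 − 0.97^18 = 42.2% |

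Ratio of glibenclamide to dapagliflozin when the true daily risk is identical:

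- 1-day window: 13.1 to 16.5 at p = 1%, and 11.6 to 14.1 at p = 3%, so about 12- to 17-fold.
- 3-day window: 4.4 to 5.6 at p = 1%, and 4.0 to 4.8 at p = 3%, so about 4- to 6-fold.

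A Poisson version, P = 1 − exp(−rate × days), over assumed rates of 0.005 to 0.10 events per person-day gives 17.3 down to 7.9 for a 1-day window.

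**Step 3: clustering at the clamp.** Each glibenclamide step and the dapagliflozin step contains one clamp. If the clamp adds a common risk q, then P(any) = 1 − (1 − q)(1 − p)^d. As q rises, the percentages in the two windows move closer and the ratio falls towards 1. The figures in step 2 correspond to q = 0.

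**Step 4: glibenclamide doses against each other.** Even if every participant had 18 days on one dose and 14 on another, the ratio would be 16.5/13.1 = 1.26 at p = 1% and 42.2/34.7 = 1.22 at p = 3%. Over the wider Poisson range it is 1.11 to 1.27.

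**Step 5: would event counts alone be enough?** No. Expected events are 20 × rate × days. At an assumed 0.02 per person-day, that is 20 × 0.02 × 14 = 5.6 to 20 × 0.02 × 18 = 7.2 per glibenclamide dose, against 20 × 0.02 × 1 = 0.4 for a 1-day dapagliflozin window. Dividing by participant-days (280 to 360 against 20) returns 2 per 100 participant-days in each case.

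**The case against.** The strongest reply is that safety here is descriptive. The SAP plans no test, contrast or ranking of one drug against the other, and the percentage of subjects with any event is a conventional summary for an open-label pilot with 20 treated participants. A reader can also see from the design that dapagliflozin is one dose. This stands in part. A reader might infer that the plan contains a biased safety comparison; it does not. The risk lies in how adjacent columns are read.

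Secondly, the list of tables is not expressly exhaustive, and the lines give counts as well as percentages of subjects. It would therefore go too far to say that events will never be reported or that only percentages are planned. But a defined endpoint should not depend on a table that is not listed.

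Thirdly, the window for attributing events may be set in the protocol, which is not at hand, and a constant daily hazard fits poorly with a design whose most stressful procedure is the clamp. Both points stand. They limit the size that can be claimed, but they do not alter the fact that time at risk is absent from the tables.

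Two further inferences are tempting and not supported. One is that comparison between glibenclamide doses is distorted: all three share the same 14-18 day range and are given in randomised sequences, and step 4 shows a small effect even at the extreme. The other is that an untreated column is required: section 2.2.2 limits the endpoint to treatment periods, so leaving out step 1 is consistent with it.

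**Conclusion.** The point holds on two counts. The endpoint defined in section 2.2.2 is not among the tables listed in section 5.4.4, and this follows from the text alone. The by-treatment percentages for glibenclamide and dapagliflozin are also not comparable, because the windows differ and no time at risk is given. The direction of that distortion is clear if risk accrues over time. Its size is not known: 12- to 17-fold needs a 1-day window and a constant 1-3% daily risk, a 3-day window brings it to 4- to 6-fold, and events concentrated at the clamps would reduce it further. Primary and exploratory analyses are not affected.

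**What to change.** In section 5.4.4:

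- Add, for each of 0.3 mg, 0.6 mg, 3 mg and dapagliflozin, the number of events, the participant-days at risk and the events per 100 participant-days, beside the subject counts and percentages.
- State, or cross-refer to, the period over which events are attributed to each treatment, including the washout and the time after the dapagliflozin dose.
- Note that glibenclamide and dapagliflozin percentages are not directly comparable.

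A column for the untreated first step is optional.

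The cost is a few table columns and some wording, provided event onset and dosing dates are recorded. That is an assumption, since the SAP does not say so. There is also a limit to what the rates can show. With 20 participants and a 1-day window, a single event equals 1/20 × 100 = 5 per 100 participant-days; with a 3-day window it is 1/60 × 100 = 1.7. The dapagliflozin rate will be imprecise and should be presented as such.
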